## Background

The World Health Organization ranks major depressive disorder (MDD) among the most debilitating diseases to society, partly due to its association with increased utilization of healthcare resources, diminished quality of life, and indirect personal and societal costs [1]. More than 50% of patients with MDD do not reach remission with initial treatment; of those 30–50% are unresponsive to treatment [2]. The designation “treatment-resistant depression (TRD)” is used to describe patients who do not respond to antidepressant therapy despite the use of appropriate dosages in one or more adequate trials of at least 6 weeks duration [3], which contributes to a disproportionately high burden of illness. The treatment of choice hereafter has traditionally been electroconvulsive therapy (ECT). Although effective, this method of neuromodulation can have a deleterious effect on the cognitive function of patients during the course of treatment [4].

Another promising neuromodulatory method that may be used in this scenario is transcranial direct current stimulation (tDCS). Unlike ECT, tDCS consists of the application of a low-intensity current for longer periods (typically 20–30 min) through electrodes that are applied to the scalp. Previous results have suggested that tDCS may be an effective treatment for MDD; however, its role in treating TRD remains unclear. A meta-analysis by Brunoni et al. (2016) [5] found that the likelihood of response to tDCS was positively correlated with treatment duration and dose but negatively correlated with treatment resistance (defined as a failure to respond to two previous trials of antidepressants). To date, some studies [6–10] have specifically examined the use of tDCS in patients with TRD; all were limited by their small sample sizes and relatively low-intensity protocols, among other methodological issues.

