### Sample size

The sample size was calculated based on the data from O’Doherty et al. (2001) [11] and Cieslik et al. (2013) [16]. In these studies, active tDCS was assumed to be superior to sham tDCS in controlling depression with a conservative mean difference of 0.65 and standard deviation (SD) = 0.25. We set a type 1 error α (significance) and a power of 80%. The G power software (V3.1.9.4) was used to calculate the sample size. The results indicated a minimum requirement of 24 participants per group (a total of 72 participants). Accounting for a 20% dropout rate, 87 participants are required for our experiment. Finally, we plan to enroll 30 participants per group for a total of 90 participants.

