### Statistical methods

Descriptive analyses will consist of means and SD for continuous variables and percentages for categorical variables. Data normality will be tested with the results expressed as mean ± SD or percentage, whenever appropriate. Nonparametric tests are to be used if the data are not normally distributed. Baseline variables will be compared between the groups using either the Student’s t-test or chi-squared test (e.g., sociodemographic data, cognitive function data, biomarkers representing inflammatory mechanisms associated with TRD, and response and remission rates among groups). To compare the primary endpoint, a two-way ANOVA will be used, considering the group (intervention and sham control groups) and time points (pre- and post-intervention), followed by the Bonferroni post hoc test, in case of significant F-ratios. A mixed-effects model for repeated measures will analyze changes from baseline HAMD-17 scores, time, and their interaction. Pretreatment values (e.g., age, sex, baseline HAMD-17, and biomarker levels) will be adopted as covariates to correct for possible differences. An intention-to-treat analysis will be conducted, that is, all participants will be included in the final analysis regardless of adherence to the intervention. No additional analyses will be performed for this study. All calculations are to be performed using R software (version 4.1.3), and the significance level is set at *p* ≤ 0.05.

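### The sample-size inputs as printed (difference 0.65, SD 0.25, 80% power, no numeric alpha) do not reproduce 24 per group, and 87 is the wrong allowance for 20% dropout

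*Protocol article*

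**What the plan says.** All the planning figures are in the Sample size section of the protocol article. Active stimulation is assumed to beat sham by a "conservative mean difference of 0.65 and standard deviation (SD) = 0.25". The scale is not given: it could be HAMD-17 points, the proportional reduction in HAMD-17 that is the primary outcome, or standard-deviation units. On error rates the section says "We set a type 1 error α (significance) and a power of 80"%, with no value for alpha. The only numeric level is in Statistical methods: "the significance level is set at *p* ≤ 0.05", with sidedness not stated. G*Power is named as the software, but the test is not named.

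The result is "The results indicated a minimum requirement of 24 participants per group (a total of 72 participants"). The next step reads "Accounting for a 20% dropout rate, 87 participants are required for our experiment". Enrolment is then set at 30 per group, 90 in total.

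**The concern.** A sample-size statement should let a reader put the inputs into the stated method and obtain the stated number. Here the difference, SD, power and result are all printed, and they do not agree under the obvious calculation. This is more than an article leaving detail to a fuller document, because no added detail makes a difference of 0.65 with an SD of 0.25 call for 24 per group in a comparison of two means.

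What is at stake is the meaning of the 80%. If the effect that the trial was sized for is unknown, a non-significant result cannot be read against it: nobody can say which difference the trial was likely to detect. The dropout step is a separate and smaller slip in the same paragraph.

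**Working it through.** **Inputs.** From Sample size: difference 0.65, SD 0.25, power 80%, 24 per group (72 in total), dropout 20%, 87 required, 90 enrolled. From Statistical methods: level 0.05. Assumption: two-sided testing, since sidedness is not stated.

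**Attempt to reproduce 24 per group (two-sample t-test).** The normal approximation is n per group = 2(z₀.₉₇₅ + z₀.₈₀)²/d², with (1.960 + 0.842)² ≈ 7.85. The exact figure uses the noncentral t distribution with 2n − 2 degrees of freedom and noncentrality d√(n/2).

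| Reading | d | Normal approximation | Exact t-test |
|---|---|---|---|
| Literal: 0.65 with SD 0.25 | 0.65/0.25 = 2.6 | 15.70/6.76 = 2.3, so 3 | 4 (power 86%; 3 per group gives 67%) |
| 0.65 is already standardised | 0.65 | 15.70/0.4225 = 37.2, so 38 | 39 (power 81%; 38 per group gives just under 80%) |

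Neither gives 24. One-sided testing at 0.05 with d = 0.65 gives 30. Splitting alpha over two active-versus-sham comparisons (two-sided 0.025) gives 47.

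**Three-group one-way ANOVA at 0.05.**
- f = 1.23 (from d = 2.6, both active arms equal): 4 per group.
- f = 0.306 (from d = 0.65, both active arms equal): 36 per group.
- f = 0.25: 53 per group.
- f = 0.65: 9 per group.

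**Settings that do reach 24 per group.** Each needs something that the section does not state.
- Repeated-measures ANOVA, between-group test, f = 0.65/2 = 0.325, 3 groups, 2 measurements, correlation 0.5: power 0.784 at N = 69 and 0.803 at N = 72, so the minimum is 72.
- The same test with f = 0.306, 3 measurements, correlation 0.5: also 72.
- The same test with f = 0.25, 4 measurements, correlation 0.25: also 72.
- Two proportions, 0.65 versus 0.25, two-sided 0.05: 23.07, so 24 per group. This contradicts the description of the inputs as a mean difference and an SD.

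Several different set-ups give the same number, so the number does not identify the one that was used.

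**What 24 per group detects.** Solving the exact t-test for 80% power gives d = 0.83 at two-sided 0.05 and d = 0.92 at two-sided 0.025.

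**Dropout.**
- Reproduced: 72 × 1.2 = 86.4, which rounds up to the stated 87.
- Check: 87 × 0.8 = 69.6 completers, below the stated minimum of 72.
- Correct step: 72/(1 − 0.2) = 90, or 30 per group, and 90 × 0.8 = 72.

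**The case against.** The strongest reply is that the article never names a two-sample t-test. Its primary analysis is a two-way ANOVA of group by time, and a repeated-measures calculation with f = 0.325 and a correlation of 0.5 gives exactly 72. This stands in part: 24 may come from a legitimate run, so one cannot say that no basis exists. But that set-up leaves the SD of 0.25 unused, applies a two-group conversion (f = d/2) to three groups, and relies on a correlation that is nowhere given. It does not make the printed inputs yield the printed result.

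A reader might infer that the trial is underpowered. At d = 0.65 an unadjusted two-sided 0.05 t-test has about 60% power with 24 per group and 70% with 30. The documents do not support that conclusion, for two reasons. On the literal reading, 24 per group is far more than needed. One may find that reading implausible, because on a proportional-reduction scale 0.65 would be 65 percentage points, but no scale is stated and so the other reading is not established. Also, Statistical methods plans baseline HAMD-17 as a covariate. If baseline correlates 0.3 to 0.7 with outcome (an assumption), power at d = 0.65 becomes about 64% to 87% with 24 per group and 74% to 93% with 30.

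A reader might also dispute the word conservative, because the Background reports that response to tDCS is "negatively correlated with treatment resistance (defined as a failure to respond to two previous trials of antidepressants"), close to the population enrolled. The same sentence says that response rises with treatment duration and dose, and this regimen is described as intensive. No magnitude is given for either, and the 0.65 is attributed to cited studies that are not at hand, so the word cannot be judged from the article.

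Finally, the dropout slip has no practical effect on enrolment. That is correct.

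**Conclusion.** The point holds in a limited form. The stated 24 per group does not follow from the stated inputs: a two-sided 0.05 t-test needs 4 per group on one reading and 39 on the other, and 24 appears only with a test, effect-size conversion, number of measurements or correlation that the article does not report. The 80% power is therefore not derivable from what is written. Whether the real power is above or below 80% cannot be determined, since the two readings lie on either side of 24.

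The 87 is a wrong figure, but planned enrolment of 90 is exactly what 20% loss requires, so no patient numbers change.

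The t-test figures assume two-sided testing, equal groups and no covariate adjustment. The 0.025 figures assume an equal split of alpha over two active-versus-sham comparisons. The article does not specify such a split in the sample-size calculation; it mentions Bonferroni only for post hoc tests after a significant F-ratio.

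**What to change.** Keep 90 participants and replace 87 by 90, shown as 72/0.8. Then do one of the following.

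1. If the original G*Power run can be retrieved, correct the inputs to match it: test, effect size and its scale, SD, numeric alpha with sidedness, number of measurements and assumed correlation.
2. If it cannot, remove the 0.65/0.25 pair and state what 24 evaluable per arm detects with 80% power: a standardised active-versus-sham difference of about 0.83 at two-sided 0.05, or about 0.92 at two-sided 0.025 if alpha is split over the two comparisons, in both cases before any gain from baseline adjustment. Express this difference on the primary HAMD-17 scale and give the SD used.

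The second route discloses what a fixed sample size can detect; it does not justify that effect as a planning assumption, and the text should say so. Either route costs wording only and adds no patients. The downside is that the stated detectable effect may look less favourable than the present text suggests.

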### Recruitment

A well-trained group will be involved in the participant enrollment process, including one senior psychiatrist, one PhD student, one MD student, eight master’s students working full-time, and ten psychiatrists who referred patients for scientific research. Participants and their guardians will be provided with a thorough explanation to ensure that they fully understand the study.

The Shanghai Mental Health Center is one of the two largest mental health facilities in China, with approximately 600,000 outpatients every year and 1300 beds. We will be sure to complete the study schedule using the current protocol.

### Treatment allocation

Patients were randomly assigned to one of three groups: the active DLPFC tDCS group, active OFC tDCS group, or sham tDCS group based on a computer-generated randomization scheme (REDCap) stratified by the study staff and assigned as groups A, B, or C. Participants will not be able to accurately guess what treatment they would receive. The clinician scales are to be administered by trained and blind study staff to ensure consistency. Moreover, the internal consistency of all psychiatrists involved in the scale ratings will be checked to ensure a kappa value of 0.89.

Two senior psychiatrists familiar with the DSM-5 criteria, will guarantee an accurate diagnosis. All patients who fulfill the inclusion criteria will be randomized. Randomization will be requested by psychiatrists responsible for recruitment and clinical interviews.

### Blinding

The staff responsible for the recruitment and symptom evaluation will be blinded to the information regarding the group allocation. A staff member outside the research group will feed the data into a computer.

### Data collection methods

#### Primary study parameter/endpoint

*HAMD-17*: The primary outcome criterion is the reductive ratio of the HAMD-17 score after one, two and 4 weeks of treatment. Treatment response is defined as a 50% reduction in the HAMD-17 score, and remission as a 75% reduction at any point during the 12-week trial compared with the baseline.

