**Methods:**

Ninety eligible participants will be recruited to receive intervention at Shanghai Mental Health Center. Treatment will be randomly assigned in a double-blind fashion. Participants will receive either DLPFC (*n* = 30), OFC (n = 30), or sham (n = 30) tDCS, while continuing their usual pharmacotherapy at a stable dosage for at least 2 weeks before enrollment and throughout the stimulation period. All participants will receive 20 weekday stimulation sessions of 60 minutes duration each. Participants in the active group will be stimulated at 2 mA throughout the session, whereas the sham group will receive only a brief period of stimulation to mimic the sensation. After 20 stimulation sessions, no further treatment will be administered. Measurements will be conducted at regular points throughout and at 8 weeks after trial completion. The primary outcome is the change in the 17-item Hamilton Depression Rating Scale (HAMD-17) score after 20 sessions. Secondary outcomes were defined as changes in other measurement scales, cognitive function, resting-state functional magnetic resonance imaging (rs-fMRI), and serum biomarkers.

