**Discussion:**

We hypothesize that, in contrast to the sham group, both the active DLPFC and OFC tDCS groups will show superiority in HAMD-17 score reduction after 5, 10, and 20 sessions. Moreover, associations of the improvement of depressive symptoms with variations in rs-fMRI and TRD-related biomarkers will be evaluated. Our study may suggest that adjunctive intensive tDCS with left DLPFC positive stimulation or right OFC negative stimulation may be effective as a novel method to relieve depressive symptoms in patients with TRD. The variation of rs-fMRI, biomarkers could be used as a potential prediction model of treatment efficacy in TRD.

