### Outcomes

Primary outcome: The reductive ratio of HAMD-17 after 4 weeks, as well as after 20 sessions.

Secondary outcomes: The changes in other clinical assessments such as the Young Mania Rating Scale (YMRS), Clinical Global Impression Scale (CGI), cognitive function, biomarkers representing potential mechanisms associated with TRD, and neuronal activity measured using rs-fMRI.

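### The primary outcome is stated inconsistently (score change or reductive ratio; end of course only, or weeks 1, 2 and 4), and the analysis section does not settle which version decides

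*Protocol article*

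**What the plan says.** Four places in the protocol article bear on what the primary outcome is:

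- Abstract, Methods: "The primary outcome is the change in the 17-item Hamilton Depression Rating Scale (HAMD-17) score after 20 sessions".
- Outcomes: "The reductive ratio of HAMD-17 after 4 weeks, as well as after 20 sessions".
- Data collection methods, Primary study parameter/endpoint: "The primary outcome criterion is the reductive ratio of the HAMD-17 score after one, two and 4 weeks of treatment".
- Abstract, Discussion, on the hypothesis for both active groups: "will show superiority in HAMD-17 score reduction after 5, 10, and 20 sessions".

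Statistical methods assigns the primary endpoint a two-way ANOVA, specified as "considering the group (intervention and sham control groups) and time points (pre- and post-intervention". Its multiplicity step is described separately: "followed by the Bonferroni post hoc test, in case of significant F-ratios". The section then adds a second model: "A mixed-effects model for repeated measures will analyze changes from baseline HAMD-17 scores, time, and their interaction". The threshold is given once: "the significance level is set at *p* ≤ 0.05". Baseline HAMD-17 is listed among the covariates.

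**The concern.** The versions differ in two ways.

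**Form.** The abstract uses a change in points. The two outcome sections in the body use a ratio. These are not interchangeable, because the ratio divides by the patient's own baseline and entry requires only a score of at least 17. The same improvement in points therefore counts for more in a patient who starts lower, and patients can rank differently on the two scales.

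**Timing.** The abstract and the Outcomes section point to the end of the course. The endpoint section lists three visits, and the hypothesis names the same three (5, 10 and 20 weekday sessions are nominally weeks 1, 2 and 4).

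With no governing version, no deciding model and no rule for combining visits, the primary result could be chosen after the data are seen. The interim analyses in the Data monitoring section are also defined on the primary endpoint, so they inherit the ambiguity.

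**Working it through.** **Step 1. Set the definitions against the analyses.**

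| Place | Form | Time |
|---|---|---|
| Abstract, Methods | score change | end of 20 sessions |
| Outcomes | ratio | 4 weeks / 20 sessions |
| Primary study parameter/endpoint | ratio | weeks 1, 2 and 4 |
| Abstract, Discussion (hypothesis) | score reduction | 5, 10 and 20 sessions |
| ANOVA, Statistical methods | score (see below) | pre and post only |
| Mixed model, Statistical methods | change from baseline | visits not named; no contrast singled out |

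Take the ratio as (baseline − follow-up) / baseline, which is how the endpoint section treats response. It is then zero for everyone before treatment. A pre/post ANOVA therefore fits raw scores, not the ratio, and the mixed model is on change. No analysis of the ratio is named. The ANOVA has two time levels, so its Bonferroni step cannot supply a rule across weeks 1, 2 and 4.

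**Step 2. Show what the form changes.** A fall of 9 points from the entry minimum of 17 is 9/17 = 53%. From an illustrative baseline of 30 it is 9/30 = 30%. The same point change falls on opposite sides of the protocol's 50% response line.

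**Step 3. Show what the timing could cost.** The protocol states no family-wise error figure to reproduce. The inputs are:

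- From the document: level 0.05, 1:1:1 allocation to two active arms and one sham arm, and three visits.
- Assumed: two-sided tests, normal test statistics, no true effect, a common between-visit correlation ρ, and success at any one visit being enough.

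For active arm k at visit t, Z(k,t) = [g(k,t) − g(sham,t)] / √2. Each g is standard normal with correlation ρ between visits. The shared sham arm makes the two comparisons correlate at 0.5 within a visit. Check at ρ = 0 for one comparison: 1 − 0.95³ = 14.3%; the simulation gives 14.2%.

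Results from 1,000,000 draws:

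| ρ | One comparison, 3 visits, 0.05 each | Two comparisons, 3 visits, 0.05 each | Two comparisons, 3 visits, 0.05/2 = 0.025 each |
|---|---|---|---|
| 0 | 14.2% | 24.8% | 13.3% |
| 0.3 | 13.6% | 23.7% | 12.7% |
| 0.5 | 12.6% | 22.0% | 11.9% |
| 0.7 | 10.9% | 19.2% | 10.4% |
| 0.9 | 8.4% | 14.9% | 8.0% |

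The last column is Bonferroni over the two arms only. The preliminary F-test is not modelled; requiring it could only lower these rates.

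**Step 4. Compare with a single time point.** Two active-sham tests at one visit give about 9.1% unadjusted, and at most 2 × 0.025 = 5% with Bonferroni. If all three visits stayed primary with any-visit success, Bonferroni over 3 × 2 = 6 tests would need 0.05/6 = 0.0083 per test.

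**Step 5. Take the opposite reading.** If a comparison succeeds only when all three visits are significant, its false-positive chance cannot exceed that of any one visit, so at most 5%. The visits then add no inflation; the price is power.

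**The case against.** The strongest reply is that the text converges on the end of the course. The primary objective speaks of a 4-week treatment, the abstract and the Outcomes section point there, and the primary ANOVA has only a pre and a post level. Only the endpoint section lists weeks 1 and 2 as primary. The hypothesis can be read as requiring superiority of both active arms at all three time points, which would inflate nothing. A Bonferroni step is stated, and an analysis plan not shown here may hold a fuller multiplicity rule.

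Much of this stands. The end of the course is common to every version, which makes the repair easy. But an analysis plan cannot make the abstract and the two outcome sections of this article agree, and the reply leaves score change against ratio untouched.

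Three stronger readings are tempting and should be resisted:

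- A reader might infer that the trial runs at a 15-25% false-positive rate. The document never says that one visit suffices, so that range is conditional.
- A reader might infer that there is no multiplicity adjustment. There is one, but its family is undefined and it does not reach across visits.
- A reader might count 4 weeks and 20 sessions as separate time points. Twenty weekday sessions take 4 weeks, so they are nominally one visit and part only if sessions are missed.

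**Conclusion.** The concern holds as an internal inconsistency in the protocol article. The primary outcome differs between sections in form and in timing. The stated analyses do not analyse the ratio, do not say which model decides, and give no rule across weeks 1, 2 and 4.

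The contradiction rests on the text alone and is certain. Its statistical size is conditional. With any-visit success it is about 15-25% over both comparisons if unadjusted (ρ from 0.9 to 0), or about 8-12% with Bonferroni over the two arms (ρ from 0.9 to 0.5; 13.3% at ρ = 0). If all visits are required, the visits add nothing. The correlations are assumptions.

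A reader might also infer that the sample size was planned for some other outcome. The Sample size section ties its inputs to no outcome form or visit, so neither a match nor a mismatch can be shown on this point.

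**What to change.** Use one definition in the abstract, the Outcomes section, the endpoint section and Statistical methods: change from baseline in HAMD-17 total at the end of the 20-session course (nominal week 4), assessed in a fixed window whether or not all sessions were delivered. Score change is suggested because it matches the abstract and the mixed model, and baseline HAMD-17 is already a planned covariate. The ratio could serve only if an analysis of it were specified.

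Name one deciding model. The end-of-course contrast from the mixed model is the natural candidate, with the ANOVA supportive or removed. Test DLPFC versus sham and OFC versus sham with family-wise control at 0.05, by the Bonferroni method already stated (0.025 each) or by Holm; the choice between them is a preference. Make weeks 1 and 2 and the reductive ratio secondary, and reword the hypothesis to match.

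The cost is a formal amendment and bringing the registration entry into line, preferably before any comparison by arm has been seen, including at an interim analysis. No new data are needed. The downside is that claims of an early effect at weeks 1 and 2 become secondary.

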### Eligibility criteria

#### Inclusion criteria

Ability and willingness to provide written informed consent to participate in the trial and undergo all necessary procedures;Age from 18 to 65 years;A diagnosis of MDD according to the Diagnostic and Statistical Manual of Mental Disorders, Fifth Edition (DSM-5), which is assessed by at least one professional psychiatrist;Han ethnicity;Right-handedness;Adequate auditory and visual ability to complete the necessary checks;A HAMD-17 score ≥ 17 [14];Insufficient response (response rate < 50%, and a reductive ratio of HAMD-17 < 50%) to two antidepressants with different mechanisms of action for at least 6 weeks at an adequate dose (e.g., clomipramine ≥150 mg/day, fluoxetine ≥20 mg/day) during the current episode;Willing to remain on maintenance pharmacotherapy for at least 2 weeks before the stimulation initiation and during the total stimulation period.

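### Remission is defined as a 75% fall in HAMD-17, so the remission rate is a stricter response rate and does not describe how ill patients are at the end

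*Protocol article*

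**What the plan says.** Under Primary study parameter/endpoint, the protocol article sets two categories on the HAMD-17. The first is response: "Treatment response is defined as a 50% reduction in the HAMD-17 score". The second follows in the same sentence: "remission as a 75% reduction at any point during the 12-week trial compared with the baseline". No section gives an absolute score for remission.

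The Inclusion criteria require "A HAMD-17 score ≥ 17" and state no upper limit, so baselines will differ between patients.

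Statistical methods names "response and remission rates among groups" among the examples of what the t-test or chi-squared test will compare, so the definition feeds a planned comparison. The primary outcome itself is continuous and also relative: "The reductive ratio of HAMD-17 after 4 weeks, as well as after 20 sessions" (Outcomes).

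**The concern.** The two categories differ only in the size of the percentage fall. What is called remission is a second, stricter response cut, and it does not fix the level of symptoms at which a patient qualifies. Because the primary outcome is also a ratio to baseline, none of the HAMD-17 endpoints named under Outcomes or Primary study parameter/endpoint describes end-state severity. A reader who meets a remission rate in the results would reasonably assume that one does.

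Two things follow. The same final score can carry opposite labels in two patients. And patients who enter near the eligibility cut must reach a very low score to qualify, so some who finish with few symptoms are reported as non-remitters. The words allowing the fall at any point in the 12 weeks are a separate weakness of the same sentence; fixing the time point alone would leave this one in place.

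**Working it through.** The protocol gives no remission rate, power or event count, so there is no figure of its own to reproduce. The check has two parts.

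**1. Thresholds, from the protocol's own numbers.** Inputs: the 75% rule (Primary study parameter/endpoint) and the entry floor of 17 (Inclusion criteria). Scores are integers, so the highest final score that counts as remission is the integer part of 0.25 × baseline.

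| Baseline | 0.25 × baseline | Highest qualifying score |
|---|---|---|
| 17 | 4.25 | 4 |
| 19 | 4.75 | 4 |
| 20 | 5.00 | 5 |
| 24 | 6.00 | 6 |
| 28 | 7.00 | 7 |
| 32 | 8.00 | 8 |
| 36 | 9.00 | 9 |

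- A final score of 5 from 17 is a fall of 1 − 5/17 = 70.6%: not remission. From 20 it is 1 − 5/20 = 75.0%: remission.
- A final score of 7 from 26 is a fall of 73.1%: not remission. From 28 it is 75.0%: remission.

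This part needs no outside cut-off.

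**2. Size, under assumptions.** The protocol gives neither a fixed cut nor a baseline distribution, so the number of patients affected cannot be derived from it. Assumed for illustration: a fixed cut of 7 or less; normal baseline with mean 21, SD 4 or mean 24, SD 5, rounded and truncated at 17; percentage fall normal with mean 55% or 40% and SD 28 points, independent of baseline; final score rounded.

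| Baseline mean | Mean fall | Meet 75% rule | End at 7 or less | Non-remitters among those at 7 or less |
|---|---|---|---|---|
| 21 | 55% | 24% | 36% | 32% |
| 24 | 55% | 24% | 32% | 24% |
| 21 | 40% | 11% | 19% | 42% |
| 24 | 40% | 11% | 16% | 32% |

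With 30 per arm, 24% against 36% is about 7 against 11 events (30 × 0.24 = 7.2; 30 × 0.36 = 10.8).

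**Near the entry cut.** At baseline 17, after rounding, a score of 4 or less needs a fall above 1 − 4.5/17 = 73.5%, and a score of 7 or less a fall above 1 − 7.5/17 = 55.9%.
- Mean fall 55%: the probabilities are 0.254 and 0.487, so 1 − 0.254/0.487 = 48% of those at or below 7 are labelled non-remitters.
- Mean fall 40%: they are 0.116 and 0.285, which gives just under 60%.

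**At the other end.** With a mean fall of 55%, patients who meet the 75% rule but end above 7 are 0.02% of all patients (baseline mean 21) or 0.3% (mean 24).

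**Contrast between arms.** Take 55% as the active and 40% as the sham mean fall, with 30 per arm and baseline mean 21. The difference divided by its standard error is
- 75% rule: (0.244 − 0.109) / √(0.244 × 0.756/30 + 0.109 × 0.891/30) = 0.135/0.097 ≈ 1.4;
- cut of 7: (0.361 − 0.188) / √(0.361 × 0.639/30 + 0.188 × 0.812/30) = 0.173/0.113 ≈ 1.5.

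At baseline mean 24 the values are again about 1.4 and 1.5. The odds ratios are about 2.6 under the 75% rule and 2.4–2.5 under the fixed cut.

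**The case against.** The strongest reply is that this is a preference. The protocol states an explicit rule in advance, nothing else in the article contradicts it, and a relative criterion matches the relative primary outcome. The cut of 7 comes from outside the document, so any count of misclassified patients is measured against a standard that the review supplies. Remission is not listed under Outcomes or among the secondary endpoints, and neither the primary comparison nor the sample size uses it. Both arms are judged by the same rule, and the contrast barely moves.

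Much of this stands: the consequence is limited, and the percentages are illustrative. It does not remove the structural fault, which follows from the 75% rule and the entry floor alone. A rate called remission that is compared between groups should say something about the state patients reach.

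Two stronger readings are tempting and are not supported.
- A reader might infer that the remission rate depends on the baseline mix of each arm. In the simulation the 75% rate is 24% at both baseline means, and 11% at both with the smaller fall. It is the fixed-cut rate that moves (36% against 32%, 19% against 16%). This stability comes from assuming the percentage fall to be independent of baseline, but the document offers no basis for the opposite.
- A reader might infer, from a pair such as 36 to 9 (remission) and 17 to 5 (not), that severely ill remitters commonly keep clear symptoms. The pair is arithmetically correct, but such cases are at most about 0.3% of patients with a 55% mean fall, which in a trial of 90 is close to none.

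**Conclusion.** The point holds in a limited form. The planned remission rate is a response rate with a higher bar. It does not describe end-state severity, and it gives the same final score different labels according to baseline. That much rests only on the protocol's own text.

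The practical effect is strictness, greatest near the entry score of 17. Under the assumed cut of 7 and the assumed distributions, the rule reports about 24% where 32–36% end at or below the cut, or 11% where 16–19% do. It labels 24–42% of low scorers as non-remitters. Another cut or another baseline distribution would change these figures.

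The continuous primary analysis, the sample size and, for practical purposes, the comparison between arms are unaffected. This is a correction that should be made to a supporting outcome; it does not threaten the trial's main conclusion.

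**What to change.** Before unblinding, amend the sentence under Primary study parameter/endpoint so that remission is a pre-specified fixed HAMD-17 total. A cut of 7 or less is one example; the sponsor should choose the value and justify it. Keep the percentage criterion for response. If the 75% fall is still wanted, report it as an additional outcome under a name that fits, such as marked response.

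The cost is one amended sentence. The HAMD-17 total is already collected, so no new data are needed. The downside is that the remission rate would no longer be comparable with any earlier series that used the 75% rule; reporting both outcomes avoids that.
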